#### Potential Mediators

Acceptance has been identified as a core mediator of treatment effect in prior smoking cessation interventions [30,41]. Acceptance of internal cues to smoke is measured via the validated Avoidance and Inflexibility Scale [42], using the mean of the three 9-item subscales that assess participants’ willingness to experience physical sensations, emotions, and thoughts that cue smoking. The items are rated on a 5-point Likert scale (ranging from 1=“Not at all” to 5=“Very willing”) and averaged, with higher scores indicating greater acceptance. A sample sensation item is “How willing are you to notice these sensations without smoking?” The items from the emotions and thoughts subscales are similar, substituting “feelings” or “thoughts” for “sensations.”

#### Potential Moderators

Potential moderators of the primary cessation outcome are assessed at baseline and include (1) sex (male vs female), (2) annual income (US <$20,000 vs US ≥$20,000), and (3) smoking intensity (≤10 vs >10 cigarettes per day).

#### Treatment Engagement and Satisfaction

Treatment engagement with each intervention is measured over the 12-month trial period. The primary engagement measure is the number of times users interact with their assigned intervention (ie, number of logins). Secondary measures of engagement are (1) the number of days from first to last use, (2) the number of unique days of use, and (3) time spent using the app. Satisfaction with the assigned apps is assessed via the 3-month follow-up study questionnaire. Example items include (1) “How useful was your assigned app for quitting smoking?” and (2) “How satisfied were you with your assigned app?”; both items are rated on a 5-point scale (ranging from “not at all” to “very much”).

#### Dissemination

To inform the development of a dissemination guide, we will conduct two sets of semistructured qualitative interviews: (1) with participants in the IndigeQuit arm who have completed the trial and (2) with AI/AN CAB members. Interviews will be conducted via secure videoconference, will last approximately 75 minutes, will be audio-recorded, and will be professionally transcribed verbatim. Participants will receive US $75 for completing the interview.

For IndigeQuit participants, we will recruit a 10% random sample (n=39) stratified by app use (no logins vs ≥1 login) and smoking status at 12 months (abstinent vs not abstinent). Interviews will follow a standardized semistructured interview guide developed collaboratively with the study CAB and a multidisciplinary team of AI/AN and non-AI/AN investigators with expertise in qualitative research, behavioral interventions, digital health, and commercial tobacco cessation. Trial data on recruitment yield, participant engagement, and satisfaction with IndigeQuit will inform interview guide development while allowing flexibility to explore emergent topics in greater depth. Example topics include (1) preferred ways to seek help for smoking cessation, (2) experiences using IndigeQuit, (3) perceptions of what makes the intervention unique, and (4) barriers to app use among nonusers.

For interviews with AI/AN CAB members representing diverse geographic regions, tribal affiliations, and professional roles (eg, Indian Health Service and tobacco control specialists), questions will focus on (1) barriers and facilitators to dissemination; (2) strategies for national dissemination to AI/AN communities; and (3) how high-performing recruitment advertisements, identified through trial data on reach and cost per randomization, could be adapted for large-scale dissemination. For example, CAB members will be asked whether messaging, imagery, cultural references, testimonials, or dissemination channels should be modified to increase relevance and engagement across diverse AI/AN communities and settings while preserving elements associated with strong recruitment performance.

Interview transcripts will be analyzed using the Braun and Clarke [43,44] reflexive thematic analysis approach [45]. Coding and theme development will be iterative and inductive, with regular discussions among the research team to promote flexibility and transparency in interpretation. Researchers will consider how their backgrounds, perspectives, and relationships with the research may influence data collection, coding, and interpretation.

Qualitative and quantitative findings will be integrated using a mixed methods approach. Quantitative data will characterize recruitment reach and efficiency, intervention engagement, satisfaction, and smoking outcomes. Qualitative data will help explain these patterns and identify perceived dissemination barriers, facilitators, and preferences. Integrated findings will be used to refine and prioritize recommendations and inform the development of the dissemination guide.

### Statistical Analysis Plan

#### Sample Size

The study sample size of 776 AI/AN adults was calculated based on conservative estimates of outcome data retention and quit rates from our secondary analysis of data from this subgroup in the iCanQuit trial [30]. As is common in smoking cessation trials, all participants with missing outcome data will be considered nonabstinent [46,47]. The study design includes 1:1 randomization of participants to treatment arms, 2-sided tests with α=.05, and estimated 12-month 30-day PPA rates of 17.1% and 10.2% in the IndigeQuit and QuitGuide arms, respectively. Under these assumptions, 80% power is achieved with 388 participants randomized to each arm.

#### Approach

Participant sociodemographic, mental health, smoking behavior, and cultural factors at baseline will be summarized for each treatment arm. Logistic regression models will be used to estimate the treatment effect for each binary smoking cessation outcome, adjusting for factors used in stratified randomization and baseline factors significantly related to the outcome [48,49]. Planned sensitivity analyses include complete-case cessation outcomes at each follow-up time point and multiple imputation [50] of missing primary outcome data at 12 months. Adjusted negative binomial regression models will be used to assess the difference between treatment arms for right-skewed count outcomes, such as the number of app sessions. Moderation of the treatment effect by sex, income, and smoking intensity will be assessed through separate adjusted logistic regression models with treatment-by-moderator interaction terms. Significant interactions will be probed with subgroup analyses to estimate the treatment effect at each value of the moderator. Finally, to test whether the effect of IndigeQuit on the primary smoking cessation outcome is mediated by changes in acceptance of cravings to smoke, we will use the PROCESS macro with bootstrap sampling to estimate the mediation effect and its 95% CI [51,52]. All statistical tests will be 2-sided with α=.05.

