#### Moderation Aim

The moderation aim is to explore whether the effect of IndigeQuit relative to QuitGuide on the primary cessation outcome differs by the following baseline factors: (1) sex, (2) income, and (3) smoking intensity.

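### Subgroup treatment effects are planned for significant interactions and not otherwise, in a trial sized for the main effect, so the exploratory moderation aim would report filtered estimates

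*Protocol article*

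**What the plan says.** The Moderation Aim is worded as exploratory: "The moderation aim is to explore whether the effect of IndigeQuit relative to QuitGuide on the primary cessation outcome differs" by three baseline factors. Potential Moderators makes each factor binary: sex, annual income split at US $20,000, and smoking intensity split at 10 cigarettes per day. The same three factors stratify the randomization.

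The Approach section fits "separate adjusted logistic regression models with treatment-by-moderator interaction terms", one model per moderator. It then states the follow-up step: "Significant interactions will be probed with subgroup analyses to estimate the treatment effect at each value of the moderator". The threshold comes from the closing sentence of that section: "All statistical tests will be 2-sided with α=.05".

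The Sample Size section concerns the main effect alone. It assumes "estimated 12-month 30-day PPA rates of 17.1% and 10.2% in the IndigeQuit and QuitGuide arms, respectively" and concludes that "80% power is achieved with 388 participants randomized to each arm". No interaction size, expected moderator split or interaction power is given.

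**The concern.** Requiring a significant interaction before claiming that the effect differs between subgroups is sound. Requiring it before estimating the effect in each subgroup is a different matter, because it makes the appearance of the estimates depend on their own size. Where power is low, two things follow. Most real differences of moderate size produce no subgroup estimates, and those that do get through are the ones in which chance widened the contrast.

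For an exploratory aim, the informative output is the estimate with its uncertainty. A bare statement that an interaction was not significant could be read as equal effects in men and women, in both income groups, or in lighter and heavier smokers. A trial of this size could not show that. Subgroup effects published only after passing the filter would also be a biased input to any later pooling with other trials.

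**Working it through.** **Inputs.** From Sample Size: quit rates 17.1% and 10.2%, 388 per arm, two-sided α = 0.05. From Approach: a Wald-type interaction test per moderator at the same α. Assumed, because the article does not give them: the size of the interaction and the split of each moderator. Covariate adjustment is ignored.

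**1. The plan's own figure.** The two-proportion formula with pooled variance and no continuity correction, at a mean rate of 0.1365 and a difference of 0.069, gives 387.4, rounded up to 388 per arm. Power at 388 is 80.06%. The stated sample size is reproduced, for the main effect.

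**2. Main effect on the model scale.**
- log OR = ln(0.171/0.829) − ln(0.102/0.898) = 0.597, so OR = 1.82.
- Variance = 1/(388 × 0.171 × 0.829) + 1/(388 × 0.102 × 0.898) = 0.01818 + 0.02814 = 0.0463, so SE = 0.215.

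**3. SE of the interaction.** With a share *s* of participants at one level of the moderator, the SE of the log ratio of ORs is 0.215 × √(1/s + 1/(1−s)). At 50:50 this is 0.215 × 2 = 0.430.

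**4. Power and exaggeration for an interaction of 0.597.** Power is P(|Z| > 1.96) when Z has mean 0.597/SE. Exaggeration is the mean absolute estimate among significant results, divided by 0.597.

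| Split | SE | Power | No subgroup estimates | Exaggeration of contrast | Ratio of ORs for 80% power |
|---|---|---|---|---|---|
| 50:50 | 0.430 | 28.3% | 72% | 1.9 | 3.3 |
| 60:40 | 0.439 | 27.4% | 73% | 1.9 | 3.4 |
| 70:30 | 0.470 | 24.6% | 75% | 2.0 | 3.7 |
| 80:20 | 0.538 | 19.8% | 80% | 2.3 | 4.5 |

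The exaggeration is unavoidable. At 50:50 the observed ratio of ORs must exceed exp(1.96 × 0.430) = 2.32 to be significant, while the assumed true ratio is 1.82.

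**5. Sensitivity to the assumed size and form.**
- Subgroup ORs of 2.45 and 1.35 (the main effect plus and minus half the interaction), 50:50: power 28.0%, or 27.5% by binomial simulation.
- Effect in one subgroup only, ORs 1.82 and 1.00, 50:50: power 26%.
- Risk-difference scale, 50:50: power 29.0%.
- Interaction twice the main effect (ratio of ORs 3.30), 50:50: power 79% with the variance held at the planned rates, 77% with ORs 3.30 and 1.00. The contrast is inflated only 1.13 to 1.15 times.

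**6. Direction of bias in each subgroup.** With true ORs of 2.45 and 1.35, the geometric-mean estimates among significant results are about 3.11 and 1.02. The larger effect is overstated and the smaller one understated.

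**7. The aim as a whole.** If the three tests are treated as independent, the chance that no moderator yields subgroup estimates is:
- no true interaction: 0.95³ = 86%;
- one interaction of size 0.597 at 50:50: 0.95² × 0.717 = 65%;
- all three: 0.717³ = 37%.

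**8. What ungated reporting would show.** At 50:50 (194 per arm in each subgroup) the subgroup SE is 0.215 × √2 = 0.304. An observed OR of 1.82 would carry a 95% CI of about 1.00 to 3.30: wide, and visibly so.

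**The case against.** The strongest reply is that the sentence says what happens after a significant interaction and does not contain the word only. The three interaction models are fitted in any case, and each yields an interaction estimate and SE whatever its P value. Nothing says these will be withheld, and a fuller analysis plan could list every subgroup effect. Testing the interaction first is also a conventional guard against spurious subgroup claims.

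Part of this stands. A reader might infer that the article forbids subgroup estimates after a non-significant result, or that interaction estimates will go unreported; it says neither. What the article does is state a rule for when subgroup effects are estimated and plan none outside it. Following that text produces filtered subgroup estimates. The guard against spurious claims is kept in full by reserving the claim, rather than the estimate, for the interaction test.

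Three stronger readings also go too far.
- A reader might take 28% as the power of this plan. It depends on an assumed interaction size and a 50:50 split, neither of which is documented. Power is about 20% at 80:20, and 77-79% at 50:50 for an interaction twice as large.
- A reader might conclude that the moderation aim will usually report no subgroup estimates. The 72-80% applies to one moderator with a real interaction of the assumed size. If all three were real, the chance of none at all is about 37%. If none were real, reporting no subgroup follow-up is what the test is meant to do.
- A reader might say that every reported subgroup effect is exaggerated. The contrast is, but the smaller effect is pulled down.

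**Conclusion.** The point holds as a minor weakness in how an exploratory aim is reported. Tying the estimates to significance, in a trial sized for the main effect, makes subgroup effects likely to be absent for a given moderator and distorted when present, unless the interaction is very large. The size of the problem rests on an assumed interaction equal to the planned main effect and on splits between 50:50 and 80:20. It shrinks markedly for an interaction twice that size, which would require the subgroup ORs to differ about 3.3-fold. The primary analysis, the sample size and the test of moderation itself are unaffected.

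**What to change.** Replace the conditional sentence in Approach with an unconditional one. From each of the three interaction models already planned, report the treatment effect with its 95% CI at both levels of the moderator, and the ratio of ORs with its 95% CI, whatever the interaction P value. State that the interaction test is the sole basis for claiming moderation.

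This costs one sentence and needs no extra participants, data or models. Data collection is expected to run to November 2028 and allocation stays concealed until it ends, so the change can be made before results by arm are known. The small downside is a few exploratory estimates with wide intervals, which must be labelled as such.

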## Results

The trial was funded by the National Cancer Institute in August 2024. As of August 2026, a total of 590 AI/AN adults who smoke commercial cigarettes had been enrolled. Data collection started in July 2025 and is expected to be completed by November 2028. Results will be disseminated through peer-reviewed publications and presentations at national and international scientific conferences.

## Discussion

### Anticipated Findings

The IndigeQuit RCT was designed to culturally adapt an effective smoking cessation app (iCanQuit) for AI/AN adults and evaluate the efficacy of IndigeQuit relative to a nontailored app (QuitGuide) among 776 AI/AN adults recruited nationwide. This project will deliver the first definitive trial of a promising digital intervention with the potential to reach AI/AN communities nationwide—a population that has long experienced disproportionate burdens of commercial cigarette smoking and smoking-related cancer mortality [13,53]. The study will advance scientific understanding of the efficacy of a culturally adapted app to support commercial smoking cessation among AI/AN individuals and evaluate its scalability for broad dissemination. If effective, this intervention could meaningfully advance health equity by providing an accessible, evidence-based tool to support commercial smoking cessation among AI/AN adults across diverse geographic settings.

### Strengths

The strengths of this trial include its rigorous randomized clinical study design with double-blind allocation and an active control condition, a fully powered sample size to detect commercial cigarette smoking cessation outcomes, and long-term follow-up to assess sustained effects. The study is further strengthened by biochemical verification of smoking status and the use of validated assessment measures. Its community-engaged approach, including community-based participatory research and an active CAB, together with community-informed cultural adaptation of the intervention, ensures relevance and acceptability. Additional strengths include nationwide recruitment, which supports generalizability, the examination of treatment mediators and moderators, and an exploratory dissemination aim to inform future uptake of IndigeQuit nationwide.

### Challenges and Potential Limitations

Potential challenges include trial recruitment, app engagement, retention, and remote biochemical verification. To support recruitment, we are implementing social media strategies proven effective in prior nationwide digital cessation trials, with ongoing CAB guidance to refine outreach and ensure cultural relevance. To enhance engagement and retention, we have implemented a multimodal survey procedure and continue to collect collateral contact information and provide tiered incentives, including preintervention incentives and 24-hour completion bonuses. Importantly, these approaches achieved a 93% follow-up rate among AI/AN participants in the iCanQuit parent trial [30,54,55]. CAB members will remain actively involved throughout to help address emerging recruitment and retention challenges. To address remote biochemical verification challenges, we applied prior qualitative research insights on key barriers and implemented a participant-centered approach to enhance engagement and reciprocity, alongside staff-supported procedures to improve troubleshooting, sample return rates, and reporting accuracy [56].

### Conclusions

The IndigeQuit app was designed to deliver evidence-based smoking cessation treatment that is culturally adapted to AI/AN communities and grounded in ACT. If effective, this intervention could offer a more scalable and culturally relevant treatment to AI/AN communities nationwide, helping to reduce smoking-related health inequities. In addition, qualitative interviews will identify key barriers and facilitators to dissemination, informing the development of a comprehensive guide to support the broad dissemination of IndigeQuit.

## Data Availability

The data will be shared upon reasonable request to [name].

## Appendix

Multimedia Appendix 1 Peer-Review Report by HPC - Health Promotion in Communities Study Section, Healthcare Delivery and Methodologies Integrated Review Group, National Institute of Cancer (National Institutes of Health, USA).

## Abbreviations

ACT: acceptance and commitment therapy
AI/AN: American Indian and Alaska Native
CAB: community advisory board
FAQ: frequently asked question
FDA: Food and Drug Administration
HIPAA: Health Insurance Portability and Accountability Act
PI: principal investigator
PPA: point prevalence abstinence
RCT: randomized clinical trial
